#### Exclusion Criteria

Patients who are recipients of a combined organ transplant with an extrarenal or islet cell transplant, previous recipients of a nonrenal solid organ or islet cell transplant, those known to be pregnant, those infected with HIV, those who have active BK nephropathy, those who have nephrotic range proteinuria, or those who are participating in other biomarker clinical trials at the time of assessment will be excluded from participation.

### Statistical Analysis

#### Sample Size Requirements

Sample size was determined using an SAS macro program, %GFR_Slope_Power, developed by Vonesh et al [14] specifically for the purpose of determining sample size or power estimates for comparing slopes between 2 treatment groups based on the linear spline mixed-effects model. An Assumption of eGFR slope change over 3 years in standard care was adopted in accordance with Vincenti et al [15]. Collectively, it is estimated that a sample of 450 patients per protocol would be required to detect a minimum total slope difference at 1.08 mL/minute/1.73 m^2^/year with 84% power, assuring that the study will be powered for a clinically meaningful difference of 5 mL/minute/1.73 m^2^/year. Conservatively assuming a 50% dropout rate and 50% loss to follow-up or missing data for end of follow-up, for this analysis, a sample size of 2000 participants should be sufficient to demonstrate a clinically significant difference in the primary outcome. Annual and as-needed review by an advisory board will halt enrollment when it is predicted that the sample size will be met.

#### Primary Analysis

The primary outcome variable defined is a change in the slope of eGFR in participants enrolled in the study compared to that of a matched cohort. Matching variables will include sex, race, time from transplant, living or deceased donor, and baseline eGFR.

eGFR will be summarized using descriptive statistics by study visit. Plots will be used as a general guideline to assess the functional relationship of eGFR over time for modeling purposes. Change in eGFR across time will be modeled using a linear mixed-effects (random intercept random slope) model.

#### Secondary Analysis

Secondary outcomes include continuous outcomes, categorical outcomes, and time-to-event outcomes. Categorical outcomes will be evaluated using a chi-square test or the Fisher exact test, when appropriate. Death-censored graft loss will be evaluated using a Cox cause-specific hazards model. A cumulative incidence curve will be used as with 95% CIs using the cumulative incidence function. Graft and patient survival will be estimated using the Kaplan-Meier method. Factors associated with the risk of graft loss and patient death will be evaluated using a Cox extended hazards model. The effect of TruGraf test results and TRAC test results on the risk of graft loss and patient death will be incorporated in the model as time-varying covariates. Patient-reported outcome measures will be assessed using scoring tools from the Patient-Reported Outcomes Measurement Information System (PROMIS) group. Cut point methods will be used descriptively for each time point based on thresholds known by the PROMIS group at that time or linkages to legacy measures, when appropriate. Comparison across time points will be carried out using Meaningful Change Methods for each PROMIS measure based on information and guidance from the PROMIS group.

### Resources and Biomarker Testing

Participants will be provided with access to a method of reporting real-time MRSB via smartphone app or the internet and instructed to answer the MRSB questionnaire whenever they are experiencing ADE or prior to clinic visits (Textbox 1). The MRSB questionnaire is based on side effects that have been considered in previously validated side effect measures and is based on a questionnaire used in a mobile health analysis that was found to reduce hospitalizations and grade 3 or higher ADEs [9].

Physicians will have access to a portal that will include an easy-to-read report of responses, simultaneously prioritizing frequent MRSB that the participant considers at least moderately troubling. Participants will also undergo OmniGraf biomarker testing based on the frequency of their standard of care laboratory testing (Table 1). Laboratory testing data are not mandated and will be collected and entered into the electronic case report forms if available in the patient record.

Medication-related symptom burden questionnaire.
**1. Do you have trembling hands?**
Not at allVery littleSometimesOftenAll the time
**1A. How troublesome is it?**
Not at allVery littleModerately troublingVery troublingExtremely troubling
**2. Do you have trouble falling or staying asleep?**
Not at allVery littleSometimesOftenAll the time
**2A. How troublesome is it?**
Not at allVery littleModerately troublingVery troublingExtremely troubling
**3. Are you having trouble with unplanned changes in weight?**
Not at allVery littleSometimesOftenAll the time
**3A. How troublesome is it?**
Not at allVery littleModerately troublingVery troublingExtremely troubling
**4. Do you have loss of interest in or the ability to perform sex?**
Not at allVery littleSometimesOftenAll the time
**4A. How troublesome is it?**
Not at allVery littleModerately troublingVery troublingExtremely troubling
**5. Do you have nausea?**
Not at allVery littleSometimesOftenAll the time
**5A. How troublesome is it?**
Not at allVery littleModerately troublingVery troublingExtremely troubling
**6. Do you have diarrhea?**
Not at allVery littleSometimesOftenAll the time
**6A. How troublesome is it?**
Not at allVery littleModerately troublingVery troublingExtremely troubling
**7. Do you have mood changes or feelings of depression?**
Not at allVery littleSometimesOftenAll the time
**7A. How troublesome is it?**
Not at allVery littleModerately troublingVery troublingExtremely troubling
**8. Do you have nervousness or anxiety?**
Not at allVery littleSometimesOftenAll the time
**8A. How troublesome is it?**
Not at allVery littleModerately troublingVery troublingExtremely troubling
**9. Do you have difficulty concentrating or remembering to do things?**
Not at allVery littleSometimesOftenAll the time
**9A. How troublesome is it?**
Not at allVery littleModerately troublingVery troublingExtremely troubling
**10. Do you have feelings of anger or irritability?**
Not at allVery littleSometimesOftenAll the time
**10A. How troublesome is it?**
Not at allVery littleModerately troublingVery troublingExtremely troubling
**11. Do you have headaches?**
Not at allVery littleSometimesOftenAll the time
**11A. How troublesome is it?**
Not at allVery littleModerately troublingVery troublingExtremely troubling

**Table 1 table1:** Schedule of assessments.

Enrollment or months post enrollment			Baseline visit (days –90 to 0)		3		6		9		12		15		18		21		24		27		30		33		36		Unscheduled visit		At workup for referral to transplant center
Visits	Details																														
Informed consent	Prior to any study-related procedures	✓																													
Assessment inclusion or exclusion criteria			✓																												
Participant’s demographics	Date of birth, sex, race, height, weight, and date of transplant	✓																													
Transplant information	Donor type and cause for renal failure	✓																													
Chemistry panel	Serum creatinine	✓		SOC^a^		SOC		SOC		SOC		SOC		SOC		SOC		SOC		SOC		SOC		SOC		SOC		SOC		SOC	
Immunosuppression medications	Name and changes in dose or medication			✓		✓		✓		✓		✓		✓		✓		✓		✓		✓		✓		✓		✓		✓	
Assessment of clinical events	Rejections, infections, graft Loss, and death	✓		✓		✓		✓		✓		✓		✓		✓		✓		✓		✓		✓		✓		✓		✓	
OmniGraf results	TruGraf and TRAC test results (if SOC laboratory tests are performed)	✓ (day 0)		✓		✓		✓		✓		✓		✓		✓		✓		✓		✓		✓		✓		✓		✓	
Patient’s medication-related symptom burden			✓		✓		✓		✓		✓		✓		✓		✓		✓		✓		✓		✓		✓		✓		✓
Biopsy information	Surveillance and for-cause: in case of rejection, type and grade			SOC		SOC		SOC		SOC		SOC		SOC		SOC		SOC		SOC		SOC		SOC		SOC		SOC		SOC	
Patient-reported outcomes	PROMIS^b^-29, PROMIS Self-Efficacy, and PROMIS Depression Scale	✓								✓								✓								✓					
Provider satisfaction			✓								✓								✓								✓				

^a^SOC: standard of care.

^b^PROMIS: Patient-Reported Outcomes Measurement Information System.

Physicians can use the MRSB and OmniGraf results as they see fit, along with other clinical laboratory tests and information; however, they will be provided with a potential framework for integrating the information into their practice (Figure 1). In short, clinicians will see participants and review the MRSB portal and clinical laboratory tests, including OmniGraf. If the clinician notes that the participant has less than ideal renal function or has an MRSB that is troubling him/her, a discussion can be had between the clinician and participant. A clinical workup for the renal function or ADE can be performed to identify other treatable causes. If it is determined that the ADE (including renal function) is caused by or exacerbated by medications that the participant is taking, the laboratory findings and OmniGraf biomarker results can be used within the clinician-participant discussion to help determine the risks and benefits of adjusting medications to mitigate the ADE. OmniGraf results can also provide additional information to clinicians regarding participants who do not have a low eGFR or ADE, assisting in their clinical decision-making or identifying participants who may be at risk of subclinical inflammation.

**Figure 1 figure1:**
[figure not shown]
Suggested framework for integrating OmniGraf and patients' medication-related symptom burden monitoring into clinical care. AMR: antibody mediated rejection; CKD: chronic kidney disease; TCMR: t-cell mediated rejection; Txp: transplant.

## Results

### Results Overview

The primary outcome measure of this study will be the slope change in renal function over time in kidney transplant recipients who are undergoing OmniGraf monitoring in conjunction with MRSB monitoring. Secondary outcome measures include the PROMIS Self-Efficacy for Managing Chronic Conditions–Managing Medications and Treatment–Short Form 4a; the PROMIS-29 Profile (version 2.1); the PROMIS Depression Scale, hospitalizations—subcategorized for hospitalizations owing to infections; treated rejections, MRSB, and the proportion of participants with overall graft survival at year 3 post transplantation; graft loss or death during the 3-year study follow-up period; and change in provider satisfaction.

### Study Endpoint Definitions and Assessment Plan

The following will be used to define and assess events within this study.

The primary endpoint is a comparison of the slope change in eGFR from baseline to the end of follow-up between the study participants and a matched control group. eGFR will be calculated using the 4-variable Modification of Diet in Renal Disease equation [16], with a sensitivity analysis performed using the Chronic Kidney Disease Epidemiology Collaboration equation [17]. Routine serum creatinine concentrations, which are measured as a part of usual care, will be utilized to estimate the GFR at baseline and at months 12, 24, and 36 post enrollment for assessments. The slope in eGFR change will be calculated for the entire follow-up for the primary outcome, with subanalyses performed between the other described time points. The matched control group will be a propensity-matched cohort from the US Medicare database.

Furthermore, we will compare the PROMIS Self-Efficacy for Managing Chronic Conditions–Managing Medications and Treatment–Short Form 4a scores at the end of follow-up relative to baseline [18]. This will measure changes in self-efficacy within the participant population—the belief that one can carry out a behavior necessary to reach a desired goal, even when a situation contained unpredictable and stressful elements. The study coordinator will provide access to the survey at baseline and at months 12, 24, and 36 post enrollment. Subanalyses will be performed among all time points.

We will then compare the PROMIS-29 Profile (version 2.1) scores at the end of follow-up relative to baseline [19]. This will measure changes in overall quality of life and satisfaction. The study coordinator will provide access to the survey at baseline and at months 12, 24, and 36 post enrollment. Subanalyses will be performed among all time points.

This will be followed by a comparison of the PROMIS Depression Scale scores at the end of follow-up relative to baseline [20]. This will measure changes in symptoms of depression. The study coordinator will provide access to the survey at baseline and at months 12, 24, and 36 post enrollment. Subanalyses will be performed among all time points.

Hospitalizations, subcategorized for hospitalizations resulting from infections, will be compared between study participants and a matched control group. Study coordinators will obtain information on hospitalizations and causes at all follow-up events. This will be compared to hospitalizations and causes documented within the US Medicare database for a propensity-matched control group. Hospitalizations will be defined as admission to hospital with at least one overnight stay. Length of hospital stay will also be recorded.

MRSB, as defined as the change in the number and severity of ADE self-reported by study participants, will be recorded from the end of follow-up relative to baseline.

Overall graft failure, defined as return to chronic dialysis, transplant nephrectomy, retransplantation, or death, will also be recorded. The study coordinator capturing clinical event data will review the medical record at intervals in accordance with the schedule of evaluations to determine if a study participant has developed graft failure. The timing and cause of each graft loss will be recorded for comparative analysis with the propensity-matched external cohort. Patient death will be captured in a similar manner, with timing and cause recorded as well.

The anticipated first enrollment of participants in the study is October 2022, with data analysis and publication expected in October 2027.

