## Methods

### Study Design

CLARITY is a 3-year prospective, multisite, observational study of 2000 participants with a matched control, measuring the impact of real-time patients’ MRSB and the OmniGraf biomarker panel on change in renal function over time. Approximately 50 sites will be targeted to enroll participants. The targeted sites will include transplant centers and large community nephrology practices with large populations of kidney transplant recipients who fall within the time line of 3 months to 2 years post transplantation. Sites will be limited to 200 participants to limit center effects in our outcomes.

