### Eligibility

#### Inclusion Criteria

Participants must be adult (≥18 years of age) recipients of a primary or subsequent kidney transplant, between 3 months and 2 years post transplantation, selected by their provider to undergo OmniGraf testing as part of posttransplantation care, and provide written informed consent and Health Insurance Portability and Accountability Act authorization.

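### All matched controls come from Medicare while participants are enrolled with no insurance condition, so matching cannot balance payer and any payer-related outcome difference enters the comparison

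*Protocol article*

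**What the plan says.** **Participants.** Under Inclusion Criteria: "Participants must be adult (≥18 years of age) recipients of a primary or subsequent kidney transplant". They must also be within the post-transplant window, give consent, and be "selected by their provider to undergo OmniGraf testing as part of posttransplantation care". Coverage is not mentioned. The Exclusion Criteria list clinical conditions and end with "those who are participating in other biomarker clinical trials at the time of assessment will be excluded from participation"; none concerns insurance. Study Design describes the sites the same way: "The targeted sites will include transplant centers and large community nephrology practices with large populations of kidney transplant recipients".

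**Controls.** Study Endpoint Definitions and Assessment Plan states: "The matched control group will be a propensity-matched cohort from the US Medicare database". For admissions the same section says: "This will be compared to hospitalizations and causes documented within the US Medicare database for a propensity-matched control group". Graft losses are compared with the propensity-matched external cohort, and the Abstract adds patient survival to the comparisons with the matched cohort.

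**Matching and data.** Under Primary Analysis: "Matching variables will include sex, race, time from transplant, living or deceased donor, and baseline eGFR". The demographics row of Table 1 reads "Date of birth, sex, race, height, weight, and date of transplant"; the transplant row adds donor type and the cause of renal failure. Neither list has a payer item. The primary model is a random-intercept, random-slope model, described without a payer term.

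**The concern.** The aim concerns kidney transplant recipients in general, but the comparator describes one payer's beneficiaries. Payer takes a single value in the controls and, as the eligibility rules stand, may take several in the participants. That is a different problem from a matching list that is merely short. A missing covariate can be added to the propensity model if both sources hold it. Payer cannot be handled that way, because no non-Medicare control exists to be matched.

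Without randomization, the comparative conclusion rests wholly on how alike the two groups are. If recipients with and without Medicare coverage differ in outcome after the listed matching, part of the observed contrast reflects who pays for care rather than OmniGraf and symptom monitoring. Enrolling more participants does not shrink that part; it only narrows the interval around a shifted value.

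**Working it through.** **1. The plan's own figures.** Sample Size Requirements gives 450 patients for a slope difference of 1.08 mL/min/1.73 m² per year at 84% power, with 50% dropout and 50% loss or missing data. The attrition step holds: 450/(0.5 × 0.5) = 1800, below the planned 2000, and 2000 × 0.25 = 500 remain. The 450 cannot be reproduced, because the article gives no slope SD, alpha or sidedness. Working backwards with an assumed two-sided 5% test:

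- SE of the slope difference = 1.08/(1.960 + 0.994) = 0.366.
- Implied slope SD = 0.366 × √(450/2) = 5.48 if 450 is per group, or 3.88 if 450 is the total. The SE is the same on either reading.

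**2. Why matching cannot help.** If payer were put in the propensity model, non-Medicare participants would have no possible control. They would either go unmatched or be matched while ignoring payer. Within this control source, the only way to align payer is to restrict to Medicare-covered participants, and for that their coverage must be known.

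**3. Form of the bias.** Let *s* be the non-Medicare share of participants and *D* the slope difference (non-Medicare minus Medicare) that remains after matching. With no true effect, the participants' mean slope is the Medicare slope plus *sD*, and the controls' is the Medicare slope. The expected contrast is therefore *sD*.

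**4. Illustration.** Neither *s* nor *D* is in the documents; both are assumed. The false-positive rate is Φ(*sD*/0.366 − 1.96) + Φ(−*sD*/0.366 − 1.96).

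| Non-Medicare share | D = 0.25 | D = 0.5 | D = 1.0 |
|---|---|---|---|
| 25% | bias 0.0625, 5.3% | bias 0.125, 6.3% | bias 0.25, 10.5% |
| 50% | bias 0.125, 6.3% | bias 0.25, 10.5% | bias 0.5, 27.7% |
| 75% | bias 0.1875, 8.1% | bias 0.375, 17.7% | bias 0.75, 53.7% |

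A bias of 0.25 is 23% of the 1.08 target (0.25/1.08). The rates are the same for a negative *D*, but the error then runs against OmniGraf. With 500 rather than 450 per group the SE falls to 0.347, and the 50% row at *D* = 0.5 and 1.0 rises to 11.1% and 30.2%.

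**5. Event outcomes.** If Medicare recipients had hazard ratio *H* relative to others, the apparent ratio with no true effect is roughly (1 − *s*) + *s*/*H*. At *s* = 0.5 this is 0.5 + 0.5/1.25 = 0.90 for *H* = 1.25, and 0.5 + 0.5/1.5 = 0.83 for *H* = 1.5. Both values of *H* are assumptions.

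**6. Precision of a restricted comparison.** Assume 450 per group and 500 participants remaining. Power = Φ(2.954/*f* − 1.96), with *f* = √[(450/*n*)(1 + 1/*k*)/2] for *n* participants and *k* controls each.

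- 60% Medicare-covered (*n* = 300): 67% at *k* = 1, 86% at *k* = 4.
- 50% Medicare-covered (*n* = 250): 60% at *k* = 1, 80% at *k* = 4.

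If 450 is the total (225 per group), the loss disappears in the first case: *n* = 300, *k* = 1 gives *f* = √(225/300) = 0.866 and power Φ(2.954/0.866 − 1.96) = Φ(1.45), about 93%.

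**The case against.** Four objections carry weight.

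- **Payer may be collected or used after all.** A reader might infer that payer is neither recorded nor matched. The documents do not establish that. The matching list is worded as inclusive, the propensity model is not set out in full, and Table 1 is a condensed schedule: it has no separate hospitalization row, although the text says admissions, causes and length of stay will be recorded. What can be said is that payer is absent from what is listed. This does not remove the point, because even a recorded payer cannot be balanced against an all-Medicare control group, and no restriction of participants is stated.
- **The problem may be repairable later.** To call it beyond repair at analysis would go too far. Date of birth is collected, participants give authorization for use of health information, and coordinators review medical records, so coverage might be recovered.
- **Direction is unknown.** A reader might infer that the bias flatters OmniGraf. Nothing in the documents says how slope, hospitalization or survival differ by payer. If there is no difference there is no bias; if it is reversed, the bias works against OmniGraf.
- **Size may be negligible.** With a 25% non-Medicare share and a 0.25 per year difference, the error rate stays near 5%. The high rates need a payer difference close to the 1.08 target that persists after matching on baseline eGFR, donor type and time from transplant.

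Making the Medicare-covered subset the primary contrast would also change the population the result describes and cost power. That is a reason to prefer a sensitivity analysis, not a reason to leave payer out.

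**Conclusion.** The concern holds as a mismatch between two stated choices: open enrollment by payer, and a single-payer control source. It is not a matter of detail left to an analysis plan, because no later choice of propensity covariates can balance a variable that is constant among the controls. The bias equals the non-Medicare share times whatever payer-related difference remains after matching.

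Its direction and size cannot be derived from the documents. On the stated assumptions it runs from negligible to serious: false-positive rates of about 5% to 10% at a 25% share and 6% to 28% at a 50% share, for slope differences of 0.25 to 1.0 per year. The documents do not support a claim that OmniGraf would be favored, that the inflation is large, or that payer is certainly missing from the full data collection. The plan should be changed because the exposure is open-ended and closing it is cheap.

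**What to change.** 1. Add Medicare coverage at enrollment (yes/no, and reason for entitlement) to the baseline items in Table 1. If it is not already collected for participants enrolled so far, obtain it from the medical record.
2. Prespecify a key sensitivity analysis of eGFR slope, hospitalizations, graft loss and death in participants who are Medicare-covered at enrollment. Controls should be enrolled in Medicare at the matched index date and matched on reason for entitlement, with several controls per participant where the database allows.
3. Keep the all-participant comparison, report the Medicare-covered share beside it, and state in advance what counts as disagreement between the two analyses. If they disagree, limit the comparative conclusion to Medicare-covered recipients.

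**Cost.** One form item and one further set of matched analyses; no added patients or procedures. The restricted comparison is less precise. On the 450-per-group reading its power could fall to 67% or 60% with one control each, recovering to about 86% or 80% with four. The documents do not show that four controls matched on reason for entitlement would be available for every participant.

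### The main PROMIS comparison sets end of follow-up against baseline with no control and no longitudinal model, so heavy attrition could bias it in either direction

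*Protocol article*

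**What the plan says.** Under Study Endpoint Definitions and Assessment Plan, the PROMIS Self-Efficacy short form, the PROMIS-29 Profile and the PROMIS Depression Scale share one definition: "scores at the end of follow-up relative to baseline". Surveys are scheduled at baseline and months 12, 24 and 36, and comparisons among those time points are labelled subanalyses. For self-efficacy the section adds: "This will measure changes in self-efficacy within the participant population". The Results part of the abstract likewise places the PROMIS changes in the study group, while hospitalizations, rejections and survival are compared with a matched cohort.

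The Secondary Analysis section gives the method: "Comparison across time points will be carried out using Meaningful Change Methods for each PROMIS measure". The only longitudinal model in the article is the random intercept and slope model for eGFR, under Primary Analysis.

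On attrition, Sample Size Requirements states: "Conservatively assuming a 50% dropout rate and 50% loss to follow-up or missing data for end of follow-up". It continues: "for this analysis, a sample size of 2000 participants should be sufficient". That sentence concerns the primary eGFR outcome.

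**The concern.** A contrast between the last time point and baseline, judged by change thresholds, can be computed directly only in people who have the last score. If that group is a quarter to a half of those enrolled, and staying depends on how patients feel, the result partly describes who stayed. PROMIS has no control group, so selective loss cannot cancel between arms. The article expects deaths and graft failures, and these also remove people from the final survey.

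Quality of life and self-efficacy are stated secondary objectives. A spurious shift of a few T-score points could be read as benefit or harm from the monitoring strategy when neither occurred.

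**Working it through.** **1. Participants with an end-of-follow-up score.** Inputs from Sample Size Requirements: 2000 enrolled, 50% dropout, 50% lost or missing at the end, 450 needed.

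- Losses multiplied: 2000 × 0.5 × 0.5 = 500, or 25%.
- Losses fully overlapping: 2000 × 0.5 = 1000, or 50%.
- Check against the plan: 450 / (0.5 × 0.5) = 1800 would be needed. The plan enrols 2000 and says only that this should suffice; 500 ≥ 450 agrees. The multiplied reading therefore fits the plan's sample size best, and the gap between 1800 and 2000 is rounding up, not an error.

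**2. Bias with no true change.** The document gives no PROMIS standard deviation, correlation or dropout mechanism, so these are assumptions:

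- T-score SD 10 and true mean change 0, with scores oriented so that positive means better;
- correlation ρ between baseline and month 36 of 0.5 or 0.7;
- log-odds of retention rising by 0.3, 0.5 or 1.0 per SD of better score (odds ratios about 1.35 to 2.7);
- 25% retained; 400,000 simulated patients per scenario.

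Apparent change in T-score points across these settings:

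| Retention depends on | Paired completers | Baseline-adjusted, all participants | Completers' month-36 mean minus baseline mean of all |
|---|---|---|---|
| Nothing | about 0 | about 0 | about 0 |
| Baseline score | -0.7 to -3.2 | about 0 | +1.1 to +4.5 |
| Month-36 score | +0.7 to +3.2 | +1.1 to +5.0 | +2.2 to +6.4 |

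**3. Why the paired result changes sign.** Let m be the mean, in SD units, of the score that drives retention among those retained. If baseline drives retention, completers start at 10m above average and regress to 10ρm, a change of -10(1 - ρ)m. If the month-36 score drives it, the change is +10(1 - ρ)m. At the strongest selection and 25% retained, m ≈ 0.64. This gives 10 × 0.5 × 0.64 = 3.2 for ρ = 0.5 and 10 × 0.3 × 0.64 = 1.9 for ρ = 0.7, in agreement with the simulation.

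**4. The 50% case.** With m = E[X·p(X)]/0.5, where X is standard normal and p is the logistic retention probability, m runs from 0.15 to 0.41 over the same selection strengths. Paired bias then runs from 10 × 0.3 × 0.15 ≈ 0.4 to 10 × 0.5 × 0.41 ≈ 2.1 points, in either direction. It is smaller than at 25% but does not vanish.

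**The case against.** The strongest reply is that the article fixes which scores are compared, not how missing scores are handled, and that estimators for secondary outcomes are commonly left to the full protocol or SAP. This stands in part: the lack of missing-data detail is not a fault here. But the article does state both the contrast and a method for it, puts the intermediate waves in subanalyses, and reserves a longitudinal model for eGFR. The point addresses that stated choice.

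Four stronger readings are tempting, and the document does not support them.

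- A reader might infer that dropout will appear as improvement. Only the comparison of completers' final mean with everyone's baseline mean was positive under every selection pattern tried, and the article does not plan that comparison. Its language of change within participants suits pairing at least as well, and paired bias can take either sign.
- A reader might infer that the plan itself expects a quarter of PROMIS scores. The attrition figures are a conservative allowance for the eGFR analysis, where laboratory data are not mandated; PROMIS surveys are offered on a schedule. Carrying the figures over is an inference. It is a fair one, since people who drop out also stop returning surveys, but it is not a stated expectation. The article also does not tie the end of follow-up to month 36 for PROMIS; using last available scores would include more people.
- A reader might infer that month 12 and 24 scores are thrown away. They are kept, in subanalyses, and a baseline to month-12 comparison would include people who leave later.
- A reader might infer that a mixed model cures the problem. It does so only when dropout depends on observed scores. Where the unobserved month-36 score drove retention, baseline adjustment still left +1.1 to +5.0 points.

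**Conclusion.** The concern holds in limited form. The three PROMIS endpoints rest on an uncontrolled contrast between end of follow-up and baseline. If the eGFR attrition assumption carries over and the end of follow-up means month 36, 25% to 50% of participants would supply the final score. With no true change, a paired completers' result could then lie roughly between -3 and +3 T-score points at 25% retained, and between about -2 and +2 at 50%. These sizes depend on the assumed SD, correlations and selection strengths; neither the direction nor the actual amount of bias can be read from the document. The issue concerns secondary endpoints and does not touch the primary eGFR analysis. The change is worth making because it replaces a stated method with a better one using data already scheduled.

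**What to change.** - Make the main analysis of each PROMIS measure a mixed model for repeated measures on all scheduled waves (baseline, 12, 24 and 36 months), with categorical time and unstructured covariance, and report the month-36 minus baseline contrast.
- Keep the meaningful-change thresholds as description.
- Report the completers-only change as a sensitivity analysis.
- Add a sensitivity analysis for data missing not at random.
- Show, at each wave, the numbers lost to death and to graft loss.

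The cost is analysis wording and some added analyses; no new data are collected. The drawback is that the main estimate relies on missingness at random given observed scores. It also implicitly carries scores past death, which is why deaths must be reported alongside it.
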